**Inclusion and Exclusion Criteria:**

**Inclusion criteria:** Diabetes patients (diagnosed with diabetes as designated by International Classification of Diseases (ICD-9 code 250) in the age group of  $\geq 50$  years

**Exclusion criteria:**

- a. Patients  $< 50$  years of age
- b. Distance from residence to AEH beyond 25km
- c. Already enrolled as study patients at the diabetes centre
- d. Patients screened for DR in free camps organized by the diabetes centre
- e. Diabetic patients who underwent retinal examination in the previous year prior to this intervention
- f. Patients with disability (physical or mental) who have difficulty in travelling to the eye hospital

## **Data preparation and analysis**

### *Data checking*

Data collected using the structured questionnaire forms will be entered into a custom designed data base (MS Access-2013) using double data entry. Comparison and consistency checks will be performed using Epi-info software (version: 3.4.3). The final data set will be transferred to STATA 14 (StataCorp Texas) for further cleaning and management. Variables such as age, annual income, education, distance, duration of diabetes etc. will be categorised appropriately. The paper forms will be scanned and archived for further references.

### *Outcomes*

The primary outcome will be diabetic retinopathy (DR) confirmed by dilated fundus examination at the hospital.

The secondary outcome will be hospital attendance.

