Coupling the recent advances in ophthalmology and information technology, Aravind Eye Hospitals has developed an innovative opportunistic case finding approach involving diabetes centres that binds digital retinal imaging with a robust IT solution - basically aimed at creating access for retinal screening. Telemedicine based digital retinal imaging for diabetic retinopathy has been installed in diabetes centres and the fundus images of suspected patients are sent to the Reading & Grading Centre at Aravind Eye Hospital where the images are graded using an indigenously developed software ADRES 4.0 (Aravind Diabetic Retinopathy Evaluation Software) and a report is sent back to the diabetes centre [20].

However, up-scaling this approach in India and other developing countries requires evidence about its effectiveness of achieving the desired objective. The proposed study in diabetes centres compares the effectiveness of telemedicine-based screening and hospital referral with that of a universal hospital referral strategy i.e. referring all eligible diabetic patients.

**Objective:** To compare the effectiveness of identifying Diabetic Retinopathy through referral followed by telemedicine based digital retinal imaging in Diabetes Centres with that of the a universal referral system

**Hypothesis:** Telemedicine based digital retinal imaging in a diabetes centre will identify proportionately more diabetic patients with DR and be associated with higher acceptance rates compared to Universal referral.

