### **Study Plan:**

**Design:** The design is a cluster randomised trial (RCT). Diabetes centres will be randomized to one of two strategies: telemedicine referral (TR) or universal referral (UR). Patients attending diabetes centres within a distance of 10 kms from Aravind Eye Hospital Madurai (i.e. within the urban and peri-urban area) will undergo one of these randomized interventions. A cluster RCT is required to avoid patients in the same centre being offered different screening interventions which might present both logistic and ethical difficulties.

**Procedures:** All patients identified in either arm meeting the inclusion and exclusion criteria will be referred to the clinic study coordinator who will seek fully informed patient consent (see below, under Ethical considerations) prior to enrolling the patient. Those enrolled will be counselled about DM and the importance of vision screening, and will be invited for either digital fundus imaging at the diabetes centre (TR) or for detailed examination for diabetic retinopathy (DR) at an eye hospital (Aravind Eye Hospital Madurai, AEH). Randomisation is at the level of the centre and there is no individual patient randomisation. In TR the diabetes centre will be equipped with a digital imaging system for screening the fundus and the patients diagnosed with DR or probable DR will be counselled to visit AEH for a full retinal examination to confirm (or not) the presence of

DR. In UR, the eligible patients will be counselled and referred to undergo eye examination at AEH. In both the arms the counselling and the awareness creation materials will be standardised.

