### *Strategies of analysis*

We will report two strategies of analysis for the primary outcome.

The primary intention to treat (ITT) analysis will include all patients eligible for referral in each randomised arm irrespective of compliance with referral. Eligibility for referral is defined according to the protocol, i.e. those who were offered a hospital referral. In the UR arm all patients will be offered a hospital referral. In the TR arm only those identified by teleretinal imaging as requiring further investigation or with inadequate images will be referred.

The secondary per-protocol (PP) analysis will include only patients who complied with referral (defined as attendance at Aravind Eye Hospital or at other eye specialist).

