### *Statistical analysis*

The data will be analysed using Stata14 (StataCorp Texas). All analyses will take account of the cluster trial design, i.e. the clinic/centre is the unit of randomization. The survey suite of commands ("svy") in Stata will be used for all regression models and cross tabulations.

We will first compare the distribution of characteristics between the trial arms including important prognostic covariates such as age, sex, duration of diabetes. The primary outcome will be analysed using Poisson regression comparing the proportion of DR in the TR arm with that in UR and report the risk ratio (RR) and 95% Confidence Interval (CI) in unadjusted analysis and covariate adjusted analysis. These analyses will be undertaken for the ITT and PP populations. The ITT primary outcome analysis will represent the trial main result.

For the secondary outcome we will investigate characteristics associated with hospital attendance using Poisson regression in a model including randomised arm. We will first check whether characteristics of attendance vary by randomised arm in separate analyses before combining in a single model.

We will also report descriptive analyses based on the semi structured interviews. These will be transcribed into a data base and text analysis techniques will be used to group the responses (this may necessitate translation into English if Tamil software is not available).

**Ethical consideration:** The protocol including the procedures for fully informed consent will be presented for approval from the Research Committee and the Institutional Review Board of Aravind Eye Hospital, India. Eligible participants in the telemedicine arm will be given an information sheet in the local language which will explain the purpose of the study and what

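### The hypothesis of higher acceptance has no valid test: acceptance is undefined, and hospital attendance, with no stated denominator, is not comparable between arms

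*Protocol*

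**What the plan says.** The Hypothesis paragraph makes two predictions for TR: that it finds proportionately more retinopathy, and that it will "be associated with higher acceptance rates compared to Universal referral". The second is not developed further, and acceptance is not defined.

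Under Outcomes, the only related measure is: "The secondary outcome will be hospital attendance". Neither that section nor Statistical analysis says over which patients it is calculated. The two analysis populations under Strategies of analysis are introduced for a different endpoint: "We will report two strategies of analysis for the primary outcome".

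The arms differ in who is sent to hospital. "In the UR arm all patients will be offered a hospital referral". By contrast, "In the TR arm only those identified by teleretinal imaging as requiring further investigation or with inadequate images will be referred". The Procedures paragraph adds that in TR "the patients diagnosed with DR or probable DR will be counselled to visit AEH for a full retinal examination".

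For attendance, Statistical analysis states that "we will investigate characteristics associated with hospital attendance using Poisson regression in a model including randomised arm". The Statistical Plan at the end of the document repeats this without adding a denominator or a definition of acceptance. Refusal of imaging appears only under Study Plan, as a topic for the follow-up interviews.

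**The concern.** Half of the stated hypothesis rests on an outcome that means different things in the two arms. In UR, going to the hospital is the screening offer itself. In TR, the offer is imaging at the diabetes centre, and the hospital visit is a second step for a selected minority.

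Attendance among referred patients therefore conditions on an image result that exists only in TR and arises after randomisation. Patients who know of suspected retinopathy may attend more readily whatever they think of the strategy. Attendance among all enrolled patients has the opposite problem: TR patients with a clear image are not asked to go, so a low figure can mean that TR worked as designed. Whether patients accept imaging, the step that distinguishes TR, is not measured as an outcome.

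If an arm ratio for attendance is reported, readers will take it as the answer to the acceptance question, and its size will depend on a choice that the plan does not make.

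**Working it through.** The plan states no expected attendance rate, referred share or power for attendance, so there is no figure of its own to reproduce. The check shows how far one set of data can give different answers.

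**Notation.** f = share of enrolled TR patients who are referred; a = attendance among referred TR patients; u = attendance in UR, where everyone is referred. Unprompted hospital visits by unreferred TR patients are ignored.

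- Ratio TR/UR among referred patients: a/u
- Ratio TR/UR among all enrolled patients: f × a/u

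The two differ by the factor 1/f. They fall on opposite sides of 1 only when a > u and f < u/a.

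**Referred share.** Prevalence of 12-18% is from the Rationale. Sensitivity 85-90%, specificity 85-95% and ungradable images 0-15% are assumptions, as is imaging of every enrolled TR patient.

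f = ungradable + (1 − ungradable) × [prevalence × sensitivity + (1 − prevalence) × (1 − specificity)]

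- Lowest: 0 + 1 × (0.12 × 0.85 + 0.88 × 0.05) = 0.102 + 0.044 = 0.146
- Highest: 0.15 + 0.85 × (0.18 × 0.90 + 0.82 × 0.15) = 0.15 + 0.85 × 0.285 = 0.392

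So f is about 15-39%. This is also the ceiling on all-enrolled TR attendance, even if every referred patient goes.

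**Attendance ratios.** Take a = 0.70 (assumed) and vary u, for which the protocol gives no figure:

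| u | Among referred, a/u | All enrolled, f = 0.15 | All enrolled, f = 0.30 | All enrolled, f = 0.39 |
|---|---|---|---|---|
| 0.10 | 7.00 | 1.05 | 2.10 | 2.73 |
| 0.20 | 3.50 | 0.53 | 1.05 | 1.37 |
| 0.40 | 1.75 | 0.26 | 0.53 | 0.68 |

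For f = 0.30 and a = 0.70, all-enrolled TR attendance is 0.30 × 0.70 = 0.21. The direction reverses if u is above 0.21 (and below 0.70) and does not reverse if u is below 0.21.

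**What attendance misses.** With the same f and a, and everyone imaged, the share of TR patients who complete all that they were asked to do is (1 − 0.30) + 0.30 × 0.70 = 0.91. All-enrolled hospital attendance would record 0.21 for those same patients.

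**The case against.** Four points can be made for the plan.

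- **The attendance model may be meant only to describe predictors.** It is worded as a study of characteristics, preceded by separate analyses by arm, and a risk ratio with confidence interval by arm is promised explicitly only for the primary outcome. This is fair: the text does not say that the arm coefficient will be presented as an effect. But then the acceptance hypothesis has no planned test at all.
- **A separate analysis plan may fix the denominator.** It may. Choosing between the two denominators would still not help, because neither makes attendance a comparable measure of acceptance.
- **The direction need not reverse.** A reader might infer that TR must look better among referred patients and worse among all enrolled. The documents do not support that. The Rationale expects few patients to attend under universal referral, and with u below 0.21 at f = 0.30 and a = 0.70 both ratios exceed 1. The planning rate of 30% of UR referrals diagnosed at the eye hospital would imply u of at least 0.30, but it sits poorly with the 12% prevalence in the same section, so it is weak ground for claiming reversal. What remains is that the two ratios differ by 1/f, more than threefold at f = 0.30.
- **UR patients are informed too.** It is tempting to say that patients told of an abnormality are compared with patients told nothing. Counselling and awareness materials are standardised across arms, and TR referrals include patients whose images were merely inadequate. The difference is that UR patients have no image result and have not been selected on one.

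**Conclusion.** The point holds. The acceptance hypothesis cannot be tested as planned: acceptance is undefined, uptake of imaging is not an outcome, and hospital attendance is not comparable between arms under either natural denominator. This follows from the referral rules alone and needs no assumed figure.

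The size does rest on assumptions. At f = 30% and a = 70%, the ratio is 1.75 or 0.53 if UR attendance is 40%, and 3.50 or 1.05 if it is 20%. The size of the apparent effect therefore depends on the denominator. Its direction may, but a change of direction is not certain. This is a secondary outcome and the trial's main result does not depend on it, so the change is advisable rather than essential.

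**What to change.** Define acceptance in all enrolled patients, by randomised arm, as completing the arm's screening pathway:

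- TR: a gradable image that does not need referral, or referred and attended.
- UR: attended the eye examination.

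State one rule, the same in both arms, for attendance at another eye specialist. The per-protocol definition already counts it as compliance, while the outcome is named as hospital attendance. Compare arms on pathway completion with the planned Poisson model, taking account of clustering by centre. Report hospital attendance among referred patients descriptively by arm, and do not present its ratio as an effect of arm.

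The cost is a reworded secondary outcome and one derived variable. Fundus examination details are to be recorded in both arms, and the interviews with patients who decline imaging or referral already ask about examinations elsewhere. Enrolled TR patients who decline imaging or have a clear image must stay in the analysis data set. The small downside is that hospital attendance becomes a descriptive figure.

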### *Strategies of analysis*

We will report two strategies of analysis for the primary outcome.

The primary intention to treat (ITT) analysis will include all patients eligible for referral in each randomised arm irrespective of compliance with referral. Eligibility for referral is defined according to the protocol, i.e. those who were offered a hospital referral. In the UR arm all patients will be offered a hospital referral. In the TR arm only those identified by teleretinal imaging as requiring further investigation or with inadequate images will be referred.

The secondary per-protocol (PP) analysis will include only patients who complied with referral (defined as attendance at Aravind Eye Hospital or at other eye specialist).

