A total of eight diabetes centres will be identified and four each will be randomly allocated to each arm stratified by distance from Aravind Eye Hospital Madurai. The aim of stratification is to ensure that there is no imbalance in the randomized arms in proximity to the hospital. The stratification criteria will be <5km, ≥ 5-10km. This covers the most densely populated areas (less than 5km), and the outer peri-urban/rural areas. An interviewer cum counsellor will be appointed at each of the diabetes centres in UR who will administer the consent form, collect patient data and do the referral. In the diabetes centres in TR, the interviewer cum counsellor will also be trained in fundus photography through a structured two-weeks training. The study will be carried out for a period of six months and a window of one month after referral will be given for the patient to visit the eye hospital.

At the end of the one month window after the last referral, those patients who have not complied with the referral will be contacted. A short semi structured interview will be conducted with (i) all those who decline referral and/or imaging to understand the barriers to compliance (ii) a sample of those who do attend Aravind Eye Hospital to understand the drivers of acceptance. The topic guide for the interviews will be developed from previous literature and other studies on barriers and drivers to cataract surgery uptake undertaken by Aravind Eye Hospital [21]. The results from these interviews will form a part of the final overall evaluation of the trial by adding a qualitative component. The interviewer will also ask about any other eye examinations that have been conducted by other eye professionals (ophthalmologists or optometrists) since patients may have chosen to attend elsewhere for the eye examination. In this situation information will be sought on the DR findings.

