**Sample size estimates:**

The following preliminary assumptions were made:

- (i) The proportion of patients in UR diagnosed with DR at AEH is 30% of the referred patients
- (ii) The proportion of patients in TR diagnosed with DR at AEH is 50% of the referred patients
- (iii) Power of 90% and alpha of 0.01 for a 2 sided test
- (iv) The design effect is 2 (derived from reference [4])

The estimated total sample size is 616 patients, equally distributed in each arm. Each of the 8 centres will recruit between 80 and 100 patients eligible for referral to AEH. We anticipate the time taken to recruit this number of eligible patients will be approximately 6 months. This is a conservative estimate because it is likely that a substantial number of eligible patients will be available. Population estimates show that the proportion with DR in diabetics is 12% and is higher in urban areas, in high income groups and in older people (50+) and with longer duration of diabetes [5].

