#### *Strategies of analysis*

We will report two strategies of analysis for the primary outcome.

The primary intention to treat (ITT) analysis will include all patients eligible for referral in each randomised arm irrespective of compliance with referral. Eligibility for referral is defined according to the protocol, i.e. those who were offered a hospital referral. In the UR arm all patients will be offered a hospital referral. In the TR arm only those identified by teleretinal imaging as requiring further investigation or with inadequate images will be referred.

The secondary per-protocol (PP) analysis will include only patients who complied with referral (defined as attendance at Aravind Eye Hospital or at other eye specialist).

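### The primary 'ITT' set keeps every universal-referral patient but only image-flagged or ungradable telemedicine patients, so the main risk ratio is biased upward for telemedicine

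*Protocol*

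**What the plan says.** The Strategies of analysis section, repeated word for word in the Statistical Plan at the end of the Protocol, sets the primary population: "The primary intention to treat (ITT) analysis will include all patients eligible for referral in each randomised arm irrespective of compliance with referral". It then defines the term: "Eligibility for referral is defined according to the protocol, i.e. those who were offered a hospital referral". For the two arms this means:

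- UR: "In the UR arm all patients will be offered a hospital referral".
- TR: "In the TR arm only those identified by teleretinal imaging as requiring further investigation or with inadequate images will be referred".

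The Statistical analysis section compares the proportion with DR between arms by Poisson regression in this set and calls it the main result of the trial. The Sample size section uses the same base: both assumed rates, 30% in UR and 50% in TR, are per referred patient.

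Enrolment comes earlier. The Procedures paragraph of the Study Plan has consent and enrolment first, and then: "Those enrolled will be counselled about DM and the importance of vision screening, and will be invited for either digital fundus imaging". The Study Plan also expects some patients to refuse imaging, since it will interview "all those who decline referral and/or imaging to understand the barriers to compliance". The hypothesis is that telemedicine "will identify proportionately more diabetic patients with DR". No analysis over all enrolled patients is planned, and the per-protocol set is a further subset of the referred patients.

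**The concern.** Membership of the TR analysis set is decided after randomisation, by the intervention, using a test for the outcome. TR patients with a negative image leave the denominator, including any whose DR was missed. So do those who decline imaging, because they are never offered a referral. Their counterparts in UR, who have no DR or never attend, stay in as non-cases. Adjusting for age, sex or duration of diabetes cannot undo this.

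The quantity estimated is yield per referral. The research question and hypothesis concern cases found among diabetic patients attending the clinics. Triage that is better than chance raises yield per referral even when it finds fewer cases overall. At stake is whether the main result could rank first the strategy that identifies fewer cases.

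**Working it through.** **The plan's own figures.** The planned ratio is 0.50 / 0.30 = 1.67, per referred patient. The stated total of 616 could not be reproduced with a two-sided alpha of 0.01, 90% power and a design effect of 2. That calculation gives 177 × 2 × 2 = 708; a one-sided alpha of 0.01 gives 154 × 2 × 2 = 616. This is a separate matter and nothing below depends on it.

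**Identity.** Let N patients be enrolled per arm, with C_TR and C_UR confirmed cases, and let f be the share of enrolled TR patients referred. If unreferred TR patients contribute no hospital-confirmed cases, then

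- RR per enrolled patient (RR_true) = (C_TR / N) / (C_UR / N)
- RR as planned (RR_plan) = (C_TR / fN) / (C_UR / N) = RR_true / f

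So RR_plan > 1 with RR_true < 1 whenever f < RR_true < 1.

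**The planning scenario.** 50% of referred TR patients is 0.50 × f of those enrolled. This is below UR's 0.30 whenever f < 0.60.

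**Size of f.** Inputs:

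- Prevalence p: 12-18% from the Rationale. 30% is added because a UR rate of 30% among all referred patients, non-attenders included, needs a prevalence of at least 30%.
- Sensitivity Se and specificity Sp: not in the document; assumed 80%/95%, 85%/90% and 95%/80%.
- Inadequate images u: referred under the plan's rule, but no rate is given; assumed 0% and 20%, unrelated to DR status.
- Attendance: set equal in the arms, so that only selection is at work.

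Formulas: f = u + (1 − u)[p·Se + (1 − p)(1 − Sp)]; RR_true = u + (1 − u)·Se; RR_plan = RR_true / f.

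RR_true is 0.80, 0.85 and 0.95 for the three pairs at u = 0, and 0.84, 0.88 and 0.96 at u = 20%.

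| p | Se/Sp | f, u = 0 | RR_plan | f, u = 20% | RR_plan |
|---|---|---|---|---|---|
| 12% | 80/95 | 0.140 | 5.71 | 0.312 | 2.69 |
| 12% | 85/90 | 0.190 | 4.47 | 0.352 | 2.50 |
| 12% | 95/80 | 0.290 | 3.28 | 0.432 | 2.22 |
| 18% | 80/95 | 0.185 | 4.32 | 0.348 | 2.41 |
| 18% | 85/90 | 0.235 | 3.62 | 0.388 | 2.27 |
| 18% | 95/80 | 0.335 | 2.84 | 0.468 | 2.05 |
| 30% | 80/95 | 0.275 | 2.91 | 0.420 | 2.00 |
| 30% | 85/90 | 0.325 | 2.62 | 0.460 | 1.91 |
| 30% | 95/80 | 0.425 | 2.24 | 0.540 | 1.78 |

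Hence f runs from 0.14 to 0.54, and the inflation 1/f from 1.9 to 7.1. Every RR_plan in the table is above the planned 1.67, while every RR_true is below 1.

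**One case in counts (assumed).** Take 1000 enrolled per arm, p = 18%, Se/Sp = 85/90, u = 10% and 50% attendance in both arms. UR finds 180 × 0.5 = 90 of 1000, or 9.0%. In TR, f = 0.10 + 0.90 × 0.235 = 0.3115, so 311.5 are referred. Of these, 180 × (0.10 + 0.90 × 0.85) = 155.7 have DR, and half of them, 77.85, are confirmed. That is 25.0% of those referred but 7.8% of those enrolled. RR_plan is 2.78; RR_true is 0.865.

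**Unequal attendance.** Let a be TR attendance divided by UR attendance among those referred. Both ratios are then multiplied by a. Over the table, RR_plan exceeds 1 once a passes 0.18 to 0.56 (1/5.71 to 1/1.78). RR_true exceeds 1 only once a passes 1.04 to 1.25 (1/0.96 to 1/0.80).

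**The case against.** The best defence is consistency. The sample size, the analysis set and the model all use referred patients, and yield per referral is a prespecified and useful service measure. That is true, but it supports reporting the measure, not calling it intention to treat or resting the hypothesis on it.

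A second defence is that telemedicine is expected to raise acceptance, and equal attendance rules that benefit out. This stands as a limit on the illustration: equal attendance is a null case, not a forecast. An all-enrolled analysis would credit any gain in attendance; the planned ratio cannot separate it from selection.

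Three stronger readings are tempting, and the Protocol does not support them.

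- A reader might infer that the planned ratio must exceed 1. It need not: with f = 0.335 and RR_true = 0.30 it is 0.90. The bias is upward whenever f < 1, but much lower TR attendance could outweigh it.
- A reader might take 12-18% prevalence with no inadequate images and conclude that the inflation is at least threefold. The plan refers patients with inadequate images, enrols people aged 50 or over near the city, where it says DR is commoner, and assumes 30% in UR. These bring the lower end to about 1.9.
- A reader might infer that TR centres must each recruit 80 to 100 image-flagged patients. The text is "Each of the 8 centres will recruit between 80 and 100 patients eligible for referral to AEH". Elsewhere the Protocol uses the word eligible for patients who meet the entry criteria, so this sentence can be read either way.

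**Conclusion.** The concern holds. The primary set is not intention to treat, and its risk ratio does not estimate what the hypothesis states. The ratio is biased toward telemedicine by the factor 1/f and can exceed 1 while telemedicine finds fewer cases per enrolled patient. It does not have to.

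The identity and the 0.60 threshold are arithmetic on the Protocol's own definitions and rates, given that unreferred TR patients add no confirmed cases. The ranges rest on assumed image accuracy, inadequate-image rate and prevalence: f about 0.14-0.54, inflation about 1.9 to 7 times, and, with equal attendance, a planned ratio of about 1.8-5.7 against 0.80-0.96 per enrolled patient. Because this comparison is the declared main result, it should be corrected before analysis.

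**What to change.** In Strategies of analysis and its repeat in the Statistical Plan, define the primary intention-to-treat set as all consenting eligible patients enrolled at each centre. Analyse them in that centre's arm whether or not they were imaged, referred or attended. Count every patient without hospital-confirmed DR as not identified. Keep DR per referred patient only as a descriptive referral yield.

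In Sample size estimates, state that recruitment counts enrolled patients in both arms. Restate the two assumed rates per enrolled patient, and the sample size or power that follows. This is more than a wording change, because the 50% and the 616 are both set per referred patient. At 30% prevalence the table's f of 0.275-0.54 turns the TR rate of 50% into 0.50 × f = 14-27% of those enrolled, below UR's 30%, so the planning case has to be rebuilt. The recruitment wording matters too: if the 308 per TR arm meant referred patients, about 571 (308 / 0.54) to 2200 (308 / 0.14) would have to be enrolled.

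The cost is a smaller expected effect and a less favourable stated power. No new data collection is needed, because TR patients are enrolled before imaging and the full denominator already exists.
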